### Safety outcomes

3.11

All variables related to the safety assessment of the study such as vital signs, physical examination, and various laboratory test results, including hematologic test, biochemical test, and urine test, as well as adverse events will be documented on the case report form (CRF) at every visit.

### Other instruments

3.12

Questionnaire for Sasang Constitution Classification II (QSCC II) and Korean Obesity Pattern Identification Questionnaire (KOPIQ) are the validated Korean medicine based typologies tools which helps to evaluate the efficacy and safety on different subgroups. QSCC II is a validated survey tool that diagnose into the 4 constitutional types based on the Korean traditional constitutional medicine: Taeyangin, Soeumin, Taeumin, and Soyangin. It consists of 121 items, comprising of psychological (54 items), behavioral (36 items), and physical characteristics (11 items), as well as health and disease questions (20 items).^[12]^ The result of QSCC II is automatically calculated by Win QSCC II version software (SordMedicom & sord OMS, Seoul, Korea). KOPIQ is a validated pattern identifications questionnaire on obesity which was developed by the Korean Institute of Korean Medicine (KIOM). It consists of 52 items with 4 domains: general symptoms, emotional, digestive, and vitality. The final pattern is classified by KOPIQ scoring algorithm from KIOM.^[13]^

### Statistical analysis

3.13

#### Efficacy assessment

3.13.1

The demographic data at the baseline will be analyzed using a *t* test for continuous data and a chi-square test for categorical data. Analysis of the primary endpoint will be performed using intention-to-treat (ITT) datasets. Per-protocol (PP) datasets will also be analyzed as a reference. The term ITT dataset refers to a set of data regarding all randomly assigned participants. Missing data will be assigned using the last-observation-carried-forward (LOCF) analysis method. PP datasets include data on only the participants who completed the trial with no protocol violations or deviations.

The secondary endpoint data will be analyzed using both ITT and PP datasets. The average weight change before and after treatment will be analyzed using a paired *t* test for intragroup data and a Student *t* test for intergroup data. The average weight during the treatment phase will be analyzed using repeated measures analysis of variance (ANOVA) tests. Other secondary data will be analyzed identically to the average weight change, with the exception of glucose measurements and questionnaire results, which will be compared only before and after treatment between the groups. We also use ANOVA tests to analyze subgroups of QSCC II and OPIQ. The present study has no plan for an interim analysis.

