### Subject withdrawal criteria

3.4

The subject withdrawal criteria are as follows: detection of eligibility violations; occurrence of a serious adverse event; subject has an acute reaction (such as allergy or shock) due to administration of the investigational product; detection of a systemic disease that was not discovered at the screening; <70% adherence rate; subject's withdrawal of consent; use of any forbidden medication or treatment during the trial that could affect the study result; uncooperative subject; occurrence of other significant protocol violations; subject who cannot follow up; subject unable to progress because of worsening of pre-existing disease; investigator's decision to terminate the process for the sake of the subject's health. The participants who are withdrawn after randomization will be followed up to examine outcomes.

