### Primary outcome measurement

3.9

The primary outcome is to evaluate the changes in mean body weight in the DSHT and CST groups compared with the placebo group and determine their statistical significance, if any, after 12 weeks.

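### LOCF is the only missing-data rule fixed for the primary 12-week weight analysis; with weight expected to fall in every arm, it dilutes a true difference and, if missingness differs between arms, biases it in an unknown direction

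*Protocol article*

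**What the plan says.** Section 3.9 of the protocol article sets the endpoint, assessed after 12 weeks: "The primary outcome is to evaluate the changes in mean body weight in the DSHT and CST groups compared with the placebo group". Section 3.13.1 sets the population, "Analysis of the primary endpoint will be performed using intention-to-treat (ITT) datasets", and defines it: "The term ITT dataset refers to a set of data regarding all randomly assigned participants". It then gives one rule for gaps in the data: "Missing data will be assigned using the last-observation-carried-forward (LOCF) analysis method". The only other analysis named for the primary endpoint is per-protocol: "Per-protocol (PP) datasets will also be analyzed as a reference". The per-protocol set is limited to completers without violations or deviations.

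For weight change the between-group test is "a Student *t* test for intergroup data". A repeated-measures analysis of weight is also planned among the secondary analyses: "The average weight during the treatment phase will be analyzed using repeated measures analysis of variance (ANOVA) tests".

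Three other places bear on the point. Section 3.2.1 makes agreement to a low-calorie diet an inclusion criterion. Section 3.4 lists the withdrawal reasons, among them adherence below 70%, serious adverse events, forbidden medication and lack of cooperation, and adds: "The participants who are withdrawn after randomization will be followed up to examine outcomes". Section 3.5 calls the trial a pilot that is also meant to supply the effect size for larger studies. It mentions dropout but gives no figure.

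**The concern.** LOCF assumes that weight stops changing at the last visit attended. With every arm dieting, that is implausible: weight should keep falling for much of the 12 weeks. Someone last weighed at week 4 is credited with only part of the 12-week change. Someone with no post-baseline weight is credited with none. The t test then treats these filled-in values as if they had been measured.

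Two consequences follow. If the drug effect builds up over time, a real difference shrinks even when both arms lose the same share of participants at the same times. If the arms lose different shares, or lose them at different times, a difference can appear or disappear for reasons unrelated to the drug. Unequal loss is plausible because several withdrawal reasons in section 3.4 depend on tolerability or adherence, which may differ between two herbal products and a lactose and corn starch placebo.

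The estimate is at stake as much as the test. Section 3.5 wants an effect size to plan a larger trial, and a distorted one would carry into that trial's sample size.

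**Working it through.** The plan has no figure of its own to reproduce: the 120 participants are justified by feasibility, with no SD, effect, power or dropout rate. The only design number available is 120/3 = 40 per arm (1:1:1, section 3.6).

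**Assumed inputs.** Weights at weeks 4, 8 and 12 (section 3.7 gives 4-weekly drug returns; the visit table is not shown). SD of 12-week change 3 kg. Straight-line loss. Dropouts spread equally over three last-observed points (baseline, week 4, week 8), unrelated to outcome within arm, and never weighed again.

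**Formula.** The carried values are 0, 1/3 and 2/3 of the full change, averaging 1/3. With dropout share d:

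LOCF mean = full change × [(1 - d) + d/3] = full change × (1 - 2d/3)

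**True difference -2.0 kg (placebo -2, active -4)**

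| Dropout placebo / active | Placebo mean | Active mean | LOCF difference |
|---|---|---|---|
| 20% / 20% | -2 × 0.867 = -1.73 | -4 × 0.867 = -3.47 | -1.73 kg |
| 15% / 30% | -2 × 0.90 = -1.80 | -4 × 0.80 = -3.20 | -1.40 kg (30% too small) |

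In the second row simulated power was about 53-56% with LOCF, against about 73% with a likelihood repeated-measures model.

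**No true difference (both arms -3 kg)**

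| Dropout, one arm / other | Means | Bias | Two-sided error at nominal 5% |
|---|---|---|---|
| 10% / 30% | -2.8 / -2.4 | 0.4 kg | 8-10% |
| 10% / 20% | -2.8 / -2.6 | 0.2 kg | about 6% |
| 10% / 15% | -2.8 / -2.7 | 0.1 kg | about 5% |

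**Direction.** In the 10% / 30% case, if placebo loses more, a false finding of benefit occurs in 8.9% of simulated trials, against a nominal 2.5%. If the active arm loses more, false benefit falls to 0.4%, and nearly all rejections say the drug is worse.

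**Second set of assumptions, with loss slowing over time.** Null curve -1.5, -2.5, -3.0 kg; active curve under the alternative -2.2, -4.0, -5.0 kg; SDs 1.5, 2.3, 3.0 kg; correlation 0.8 between adjacent visits; 4,000 simulated trials per case.

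- Null, equal dropout of 20% or 30%: no bias, error 0.051-0.054.
- Null, placebo 30% and active 10%: (-2.82) - (-2.50) = -0.32 kg, error 0.084.
- Null on a steeper curve (-2.0, -3.5, -4.5 kg), 20% in each arm but early on placebo and late on active: -0.70 kg, error 0.178. Timing alone is enough.
- True -2.0 kg, 20% in both arms: -1.74 kg, power 0.715 against 0.764 with the likelihood model.
- True -2.0 kg, active 30% and placebo 10%: -1.30 kg, power 0.466 against 0.768.
- True -2.0 kg, placebo 30% and active 10%: -2.19 kg, an exaggeration.

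Across the twelve scenarios of this second set, the likelihood model stayed within 0.03 kg of the true difference. Its error was 0.046-0.052 in the eight null cases.

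**The case against.** The strongest reply is that withdrawal does not by itself create a missing weight. Section 3.4 promises outcome follow-up after withdrawal, section 3.13.1 includes everyone randomised, and LOCF applies only to missing data. On a plain reading, a weight taken after withdrawal is observed and would not be replaced. This stands. A reader might infer that every withdrawn participant is frozen early, or that the plan discards the follow-up weights; the text supports neither. The figures above treat all dropouts as never re-measured, so they shrink to the extent that follow-up succeeds.

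Second, a reader might infer that the contrast is biased whenever dropout differs, or that the false-positive rate is inflated as a matter of course. Neither follows. Differences in rate and timing can offset each other. Equal dropout leaves the error near 5%, modest gaps add little, and a false finding of benefit becomes more likely only with more or earlier loss on placebo.

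Third, the comparison favours the likelihood model: simulated dropout was unrelated to outcome within arm, where that model is unbiased by design. If leavers stop the drug and then follow a different course, the model projects them along the path of those who stay and may overstate benefit. This also stands. It is a reason to add a sensitivity analysis; it does not defend LOCF.

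Fourth, this is a pilot and the analysis plan is not shown. That lowers the stakes of the test. But the article positively chooses LOCF, and the effect-size aim remains. The per-protocol analysis is no check, since it omits the participants whose values LOCF fills in.

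**Conclusion.** The concern holds in a limited form. LOCF is fixed as the sole missing-data rule for the primary analysis of an outcome expected to fall in all arms. It understates the 12-week change of anyone without a later weight. Under the assumptions above, a true 2 kg difference loses about 0.27 kg with 20% dropout in both arms and about 0.6 kg with 15% on placebo and 30% on active. With no true effect, a 20-point gap in dropout produces about 0.4 kg of spurious difference, and a 5- to 10-point gap produces 0.1-0.2 kg.

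Neither the size nor the direction for this trial can be derived from the article, which gives no dropout rate, weight curve or SD. LOCF therefore cannot be called conservative: more loss on placebo exaggerated the effect in the working. The planned repeated-measures ANOVA is not itself evidence of an error. This is a point that should be fixed; it does not invalidate the trial.

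**What to change.** In section 3.13.1, replace LOCF as the primary rule. Make the primary analysis a likelihood-based repeated-measures model of weight change at the post-baseline visits, with arm, visit, arm-by-visit and baseline weight. Report the week-12 contrast of each active arm against placebo. State that all observed weights are used, including those collected after withdrawal under section 3.4. Keep LOCF at most as a sensitivity analysis, beside one that allows for dropout that is missing not at random.

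A site term, a particular imputation scheme for that sensitivity analysis, and replacing the secondary repeated-measures ANOVA are matters of preference and are not needed to remove the defect.

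The cost is wording and somewhat more modelling work, with no extra participants or visits. The main trade-off is that the new primary analysis relies on a missing-at-random assumption, which is why the further sensitivity analysis belongs with it.

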#### Inclusion criteria

3.2.1

Criteria for inclusion of participants are as follows:

1.Females aged 18 to 65 years.2.Patients who have any of the following conditions:1)BMI 30 kg/m^2^ or over;2)BMI 25 to 29.9 kg/m^2^, who have at least one of the following risk factors;Patients who have been diagnosed with hypertension and currently under adequate treatment with antihypertensives, or individuals with systolic blood pressure (SBP) ≥140 mmHg and diastolic blood pressure (DBP) ≥90 mmHg at the screening visit.Patients who have been diagnosed with T2DM and are currently on adequate treatment or individuals with fasting blood glucose >126 mg/dL at the screening visit.Patients who have been diagnosed with hyperlipidemia and are currently under adequate treatment, or individuals with total cholesterol ≥200 mg/dL or triglycerides ≥150 mg/dL at screening visit.3.Subjects who have agreed to a low-calorie diet during the trial.4.Patients who have signed the written informed consent form.

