## Discussion

4

This multi-center, randomized, 3-arm placebo-controlled study is to investigate the efficacy and safety of DSHT and CST in female obese patients with high risk for metabolic syndrome. Findings from preclinical experiments have demonstrated the anti-obesity effects of DSHT in the presence of high glucose levels^[7]^ and CST has proved effective in increasing HDL levels. However, no previous clinical trials have reported their effects in obese patients with concomitant obesity-related diseases. Traditional herbal medicines are used widely in clinical practice for weight management in East Asia including Korea, but their use is contentious owing to the lack of high-quality scientifically-based evidence.^[14]^ Building on our study with evidence-based obesity treatment strategy for obese female patients with high risk for metabolic syndrome, this study may be the first to examine the efficacy and safety of DSHT and CST on in obese patients with high risk for metabolic syndrome.

There will be several limitations in this study. First of all, although we will obtain participants’ agreement on low calorie diet during the study period, daily food intake will not be fully controlled. Thus, participants will be encouraged to check their daily calorie intake before the clinic visits through continuous patient–researcher communication. Second, a short-term drug administration period has been applied, with small number of participants; thus, a larger, long-term trial is warranted to understand the impact on long-term weight and fat management.

In conclusion, this pilot study will provide support for the design and methods and determining the feasibility of the larger clinical trial among obese female patients in Korea. If the trial medicines are proven safe and efficacious, this study's findings will be used as an evidence for the use of DSHT and CST in female obesity treatment in Korean medicine clinics and hospitals.

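### Within-arm paired t tests are listed as efficacy analyses beside the valid between-group test, although a diet shared by all arms can make any arm significant with no drug effect

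*Protocol article*

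**What the plan says.** Section 3.13.1 of the protocol article (Efficacy assessment) states: "The average weight change before and after treatment will be analyzed using a paired *t* test for intragroup data". The same sentence goes on to name a Student t test for the comparison between groups. It stands in the paragraph on secondary endpoints. It gives the two tests equal rank: neither is called descriptive, and the article does not say which one supports a conclusion about efficacy.

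The same paragraph then says: "Other secondary data will be analyzed identically to the average weight change, with the exception of glucose measurements and questionnaire results". The excepted outcomes are those "which will be compared only before and after treatment between the groups". The paired test therefore also reaches BMI, body fat, waist and hip circumference, lipids, CRP and visceral fat, in each of three arms. The secondary endpoints are to be analysed in both the intention-to-treat and per-protocol sets.

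Two other places bear on the point:

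- **Diet.** Section 3.2.1 lists as an inclusion criterion "Subjects who have agreed to a low-calorie diet during the trial". The Discussion concedes that "although we will obtain participants’ agreement on low calorie diet during the study period, daily food intake will not be fully controlled".
- **Primary outcome.** Section 3.9 defines it as "changes in mean body weight in the DSHT and CST groups compared with the placebo group", measured after 12 weeks.

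**The concern.** A paired t test within an arm asks whether weight changed in that arm. It does not ask whether the medicine changed it. Three things move the result in every arm, placebo included:

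- the low-calorie diet that all participants agree to, followed to an unknown degree;
- regression to the mean. Women with BMI 25 to 29.9 can qualify on a high screening value, for example total cholesterol of at least 200 mg/dL or triglycerides of at least 150 mg/dL. If that reading, or one close to it, serves as baseline, a later fall in lipids is partly built in;
- the general effect of taking part in a trial.

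Only the contrast with placebo removes these shared effects. Within-arm p-values listed as efficacy results leave room for the argument that an active arm was significant, placebo was not, and so the medicine works. That argument is invalid because it never tests the difference between the arms. The number of such p-values is not small. Counting the lipid profile as one measure, there are eight measures in three arms, or 8 × 3 = 24 paired tests per analysis set and 48 over both sets.

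**Working it through.** The article gives no significance level, SD, effect size or expected diet loss, and section 3.5 justifies the sample size on logistics. There is no stated figure to reproduce. The check asks how often the paired test is significant when the medicines do nothing.

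**Inputs from the article.** 120 participants (section 3.5) allocated 1:1:1 (section 3.6) give 120/3 = 40 per arm.

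**Assumptions, not in the article.** Two-sided 5% level; the same true mean loss d in all three arms (no drug effect), from 0.5 to 2 kg; SD of change 2, 3 or 4 kg; normally distributed changes; independent arms.

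**Step 1: smallest significant loss.** The paired test is significant when the observed mean loss exceeds t(0.975, 39 df) × SD/√40. This is 0.64 kg for SD 2, 0.96 kg for SD 3 and 1.28 kg for SD 4.

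**Step 2: chance that one arm is significant.** This comes from the noncentral t distribution with 39 df and noncentrality (d/SD) × √40. For d = 1 and SD = 3, the noncentrality is 0.333 × 6.325 = 2.11 and the chance is 0.538.

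| Shared loss | SD 2 kg | SD 3 kg | SD 4 kg |
|---|---|---|---|
| 0.5 kg | 34% | 18% | 12% |
| 1 kg | 87% | 54% | 34% |
| 1.5 kg | 99.6% | 87% | 64% |
| 2 kg | 100% | 98% | 87% |

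With an assumed 20% loss of participants (32 per arm), the 2 kg row becomes 100%, 95% and 78%. At 2 kg and 40 per arm, all three arms are significant together in 0.984³ = 95% of trials for SD 3 and 0.869³ = 66% for SD 4.

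**Step 3: the misleading pattern.** Let p be the per-arm chance. Placebo is not significant and at least one of the two herbal arms is significant with probability (1−p) × [1 − (1−p)²].

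- p = 0.338 (1 kg, SD 4): 0.662 × (1 − 0.438) = 37%.
- p = 0.538 (1 kg, SD 3): 0.462 × (1 − 0.213) = 36%. Simulation of 20,000 trials gave 35.6%.
- p = 0.869 (1.5 kg, SD 3; also 2 kg, SD 4): 0.131 × (1 − 0.017) = 13%.
- p = 0.984 (2 kg, SD 3): about 2%.
- p near 1 (2 kg, SD 2): near 0%.

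With q = 1−p the expression is q − q³. It peaks at q = 1/√3 with the value 2/(3√3) = 0.385, so it cannot exceed about 38% whatever the loss or SD.

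**Step 4: the between-group test under the same conditions.** In 20,000 simulated trials with a shared 2 kg loss and SD 3, the Student t test against placebo rejected in 5.0% and 5.3% of trials for the two comparisons, and in 9.2% for either. The paired test rejected in about 98% of trials in each arm, placebo included.

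**The case against.** The strongest reply is that the valid test is already planned. The sentence that names the paired test also names the between-group Student t test, and the extension to other secondary outcomes carries that test with it. The primary outcome is set against placebo, and the paired tests stand in the secondary-endpoint paragraph of a pilot. This stands and limits the weight of the point. A reader might infer that the trial lacks a controlled comparison, or that a within-arm p-value will decide efficacy. The article supports neither.

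A reader might also link the within-arm tests to clinical use, since the Discussion foresees the findings serving as evidence for clinics. That statement is conditional on the medicines being shown to be safe and effective. The same section calls for a larger, longer trial, and nothing there rests the judgement on within-arm results.

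The two numerical results also pull against each other. When the diet loss is large enough to make nearly every arm significant, placebo is significant too, and the misleading pattern mostly disappears. A figure such as 36% is therefore close to the ceiling and is not typical of all conditions. Nor can it be said that every participant diets: the article requires agreement only and admits incomplete control.

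Finally, a fuller analysis plan might label these tests as descriptive. The point does not rest on a missing label, however. It rests on what the article does state, which is paired tests under an efficacy heading, level with the between-group test. The paragraph on the primary endpoint names no test, so this is also the only sentence that names one for before-after weight change, the primary variable. The treatment of glucose and questionnaires, though loosely worded, shows that the plan can confine itself to between-group comparison.

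**Conclusion.** The point holds as a minor to moderate defect in the secondary analyses and their interpretation. The paired tests cannot separate drug from diet or regression to the mean, and they can be significant in any arm, placebo included, when the medicines do nothing. That qualitative conclusion depends on no single assumed value.

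The size does depend on assumptions. With 40 per arm, a two-sided 5% level and an SD of change of 2 to 4 kg, one arm's paired test is significant in 34 to 87% of trials for a shared 1 kg loss and in 87 to 100% for 2 kg. The pattern of placebo not significant with at least one herbal arm significant lies between near 0% and about 38%. The placebo-controlled primary comparison is not invalidated by any of this.

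**What to change.** In section 3.13.1, replace the paired t tests with the within-arm mean change and its 95% CI, labelled as description only, for weight and for every outcome to which they now extend. Add that efficacy conclusions rest solely on the active-minus-placebo differences.

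Preferably, adjust those differences for the baseline value, which is already collected. This would replace the Student t test with a baseline-adjusted comparison. It is an improvement in its own right, and the point above does not depend on it.

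The cost is a change of wording in one paragraph, with no added data, visits or participants. The one thing given up is the reporting of within-arm p-values, which do not answer the trial's question.

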### Study design

2.1

This trial is a randomized, double-blinded, three-arm, placebo-controlled, multi-center, study that will be conducted at the following sites: Gachon University Gil Korean Medical Hospital, Dongguk University Ilsan Oriental Hospital, and Sangji University Oriental Medical Center. The total study duration is approximately 13 weeks from the screening visit. A schedule of this study flow is shown in Table 1.

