### Sample size

3.5

This trial is a pilot study to examine the feasibility of a full randomized controlled trial for evaluating the efficacy and safety of DSHT and CST in obesity and to determine the effect size for further large-scale studies. A sample cohort comprising of 120 patients have been considered after assessing their frequency of clinic visits, availability of study staff, funding availability, and dropout rates at each participating site.

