### Randomization and blinding

3.6

The Institute of Safety, Efficacy, and Effectiveness Evaluation for Korean Medicine (ISEE), the Contract Research Organization (CRO), will generate random sequences using the R program. Randomization number assignment via the web-based system will be performed at visit 2 by the clinical research coordinator (CRC) or research assistants at each site. The subjects in this trial will be assigned to one of three groups with an allocation ratio of 1:1:1. All participants, investigators, and monitors will be blinded. No one, with the exception of the statisticians at ISEE, will be aware of which random numbers refer to either of the treatment groups or the placebo group. The randomization table kept in the opaque sealed envelope by the CRO will be opened according to Standard Operating Procedures (SOPs).

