### Secondary outcome measurements

3.10

The secondary outcomes will focus on changes of following obesity related measurements between baseline and post treatment: mean weight reduction, body mass index (BMI), body fat, waist and hip circumferences, lipid profile, C-Reactive protein (CRP), volume of visceral fat, Korean version of Obesity-related Quality of Life (KOQoL), The Korean Version of Eating Attitudes Test-26 (KEAT-26).

KOQoL is a validated outpatient-based quality of life assessment questionnaire on obese patients. It consists of 6 areas (psychosocial health, physical health, work and family affairs, daily life, sexual relationships, and relationship with food) with a total of 15 items. Each item is a 4-point Likert Scale ranging from “absolutely not” (1 point) to “always” (4 points). The total maximum score is 60 points. Higher score represents low quality of life.^[10]^ KEAT-26 is a validated Korean-translated version of EAT-26. It is 6-level Likert scale which consists of 11 items concerning anorexia, 7 items concerning binging or overeating, and 8 items concerning control of eating behavior. Higher score represents more problematic mealtime behavior.^[11]^

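### Weight change and most secondary changes are compared by unadjusted pairwise t tests; ANCOVA on baseline would be more precise, by little for weight but materially for weakly tracking outcomes

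*Protocol article*

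**What the plan says.** All references are to the protocol article.

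- **Design.** Section 2.1: "This trial is a randomized, double-blinded, three-arm, placebo-controlled, multi-center, study". Section 3.6: participants are "assigned to one of three groups with an allocation ratio of 1:1:1". Three sites are named.
- **Size and aim.** Section 3.5 presents a pilot of 120 patients, a number set by feasibility, one of whose aims is "to determine the effect size for further large-scale studies". It gives no power, standard deviation or correlation.
- **Between-group test.** Section 3.13.1 analyses average weight change "using a paired *t* test for intragroup data and a Student *t* test for intergroup data". It continues: "Other secondary data will be analyzed identically to the average weight change", with glucose and the questionnaires excepted. No covariate is named.
- **Outcomes covered.** Section 3.10 defines the secondary outcomes as changes from baseline, including "mean weight reduction, body mass index (BMI), body fat, waist and hip circumferences, lipid profile, C-Reactive protein (CRP), volume of visceral fat".
- **Other analyses in the same section.** Weight over the treatment phase gets repeated-measures ANOVA, and the constitution and pattern subgroups get ANOVA.
- **Primary endpoint.** The sentences on it give the analysis set and the imputation method but no test. Both weight tests stand in the paragraph on secondary endpoints.
- **Baseline comparison.** "The demographic data at the baseline will be analyzed using a *t* test for continuous data".

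**The concern.** A change score forces the baseline coefficient to be 1. When an outcome tracks imperfectly between baseline and week 12, that coefficient is too large. Baseline noise is then added to the comparison, and any chance difference between arms at baseline carries into the estimated effect. ANCOVA estimates the coefficient from the data and so avoids both problems.

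At stake is the precision of the effect estimates, chiefly for secondary outcomes that track loosely. With the sample size fixed by feasibility, the analysis is one of the few remaining ways to gain precision.

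A related weakness is that the section does not say which weight test is the primary one. The rule also puts CRP and triglycerides on the raw scale, where right skew, if present, weakens a t test.

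**Working it through.** **Inputs.** From the article: 120 patients, three arms, 1:1:1, so 120/3 = 40 per arm. There is no stated power calculation to reproduce. Assumed: the correlation r, equal variances at baseline and week 12 (set to 1), and two-sided alpha 0.05.

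**Variance of the between-arm difference.** Per-patient variance is 2(1−r) for the change score and 1−r² for ANCOVA. The ratio is (1−r²)/[2(1−r)] = (1+r)/2, so the saving is (1−r)/2. For power, the true difference is set so that the change-score test has 80% at 40 per arm.

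| r (assumed) | Variance ratio | Variance saved | Standard error saved | Power with ANCOVA |
|---|---|---|---|---|
| 0.3 | 0.65 | 35% | 19% | 93.5% |
| 0.5 | 0.75 | 25% | 13% | 89.9% |
| 0.7 | 0.85 | 15% | 8% | 86.0% |
| 0.9 | 0.95 | 5% | 2.5% | 82.0% |
| 0.95 | 0.975 | 2.5% | 1.3% | 81.0% |

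**Cost of estimating the slope.** With 80 patients in a two-arm comparison the variance grows by roughly 1 + 1/76 = 1.013. The ratio becomes 0.75 × 1.013 = 0.760 at r = 0.5 and 0.975 × 1.013 = 0.988 at r = 0.95. At r = 0.98 it is 0.99 × 1.013 = 1.003, so the gain has gone. Simulation (6,000 trials per r, 40 per arm) gave 0.764 at r = 0.5, 0.849 at 0.7 and 0.995 at 0.95.

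**If the variances differ.** With standard deviations s0 and s1, the change-score variance minus the ANCOVA variance is s0² + s1² − 2r·s0·s1 − s1²(1−r²) = (s0 − r·s1)². This is never negative, so apart from the slope cost ANCOVA does not lose.

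**Chance imbalance.** The baseline difference between two arms has standard error √(2/40) = 0.224 SD. Given a baseline difference d, the change-score contrast is shifted by −(1−r)d. For d = 0.224 SD:

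- r = 0.5: shift 0.5 × 0.224 = 0.112 SD. The contrast has standard error √(0.05 × 1.0) = 0.224 SD, so the shift is half a standard error.
- r = 0.9: shift 0.1 × 0.224 = 0.022 SD, against √(0.05 × 0.2) = 0.100 SD, or about a fifth of a standard error.

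**Skewed outcomes.** Here the log scale and baseline adjustment must be separated. Simulated power, 4,000 trials, 40 per arm, assumed r = 0.6:

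| Outcome (assumed log-SD) | Reduction | Raw change | Log change | Log ANCOVA |
|---|---|---|---|---|
| CRP (1.1) | 30% | 17% | 35% | 43% |
| CRP (1.1) | 50% | 42% | 88% | 93% |
| Triglycerides (0.5) | 25% | 65% | 80% | 88% |

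For CRP most of the gain comes from the log scale. For triglycerides, 15 points come from the log scale and 8 from adjustment.

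**The case against.** Several objections are fair.

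- **It is matter for the analysis plan.** Covariates and transformations often are. But this section does not leave the test open: it names an unadjusted t test and extends it to most secondary outcomes. The point concerns the method stated.
- **Weight barely benefits.** This stands. At r of 0.95 or more the saving is 2.5% or less, and a pilot with no power target has none to miss.
- **The two weight tests answer different questions**, one on change from before to after treatment and one on the course during treatment. The first matches the primary outcome in section 3.9. So the documents show an unlabelled primary analysis, not an intention to choose between results.

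A reader might also infer more than the documents support:

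- *That every continuous outcome is tested this way.* The repeated-measures ANOVA, the subgroup ANOVA and the exception for glucose and questionnaires say otherwise. No test is named for the excepted outcomes, so no gain can be claimed for them.
- *That baseline is ignored.* It enters every change score with coefficient 1; only its use as a covariate is absent.
- *That up to a third of precision is lost.* One third is the variance saving at r = 1/3, about 18% on the standard error. It is not a bound, since the saving is larger at lower r.
- *That regression to the mean biases the comparison.* It acts alike on randomized arms; only chance imbalance matters.
- *That omitting the third arm or site costs much.* Pooling the variance over three arms moves the critical t only from 1.991 (78 degrees of freedom) to 1.980 (117). The gain from a site term cannot be quantified from the article.

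**Conclusion.** The point holds in a limited form. The article fixes an unadjusted pairwise t test on change for weight change and most secondary outcomes, although baseline is available and ANCOVA is the better method. The variance saving is (1−r)/2: 5% to 35% for r from 0.9 to 0.3, and 2.5% or less for weight if r is 0.95 or more. These sizes rest on assumed correlations and equal variances, since the article gives neither. Adjustment also removes the dependence on chance imbalance, which is useful when the trial is to supply an effect size.

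The log-scale advice for CRP and triglycerides rests on an assumption of right skew and is a separate gain from baseline adjustment. Nothing here shows the planned between-arm comparison to be biased or the primary result to be seriously weakened. The importance is moderate: a clear improvement, mainly for secondary outcomes.

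**What to change.** 1. In section 3.13.1, replace the between-group t test with one ANCOVA containing all three arms. The outcome is the week-12 value, with that outcome's own baseline and site as covariates. Report adjusted DSHT–placebo and CST–placebo differences with confidence intervals.
2. Name this model for week-12 weight as the primary analysis, in the text on the primary endpoint, and label the repeated-measures ANOVA as supportive.
3. Use the same model for continuous secondary outcomes. Analyse CRP and triglycerides on the log scale, report ratios between arms, and state how values below detection are handled.
4. As tidying that does not change the efficacy estimate, remove mean weight reduction from the secondary list, since it repeats the primary outcome. Replace the baseline significance tests with descriptive statistics by arm; a two-sample test does not fit three arms, and randomization already makes its null hypothesis true.

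The cost is analysis wording only, with no extra patients or measurements. The small drawbacks are the ratio-scale effect for the logged outcomes and the below-detection rule.
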